### Study procedures

Figure 2 illustrates the procedures of the trial. Once consented, participants will be asked to complete a paper- or web-based baseline questionnaire, depending on their preference, approximately 6 weeks before their next 6-monthly dermatological consultation at the HRC. Once the completed baseline questionnaire is received, the participant will be randomised into either the intervention or control group. After randomisation, 3–4 weeks before their HRC appointment, the research team will send the participant the appropriate study package, including a letter describing which group they have been randomly allocated to, and the next steps in the study. In the following week, participants in the intervention arm will be contacted by telephone by the assigned psychologist to arrange a suitable time for the first intervention session, and all three sessions will be facilitated by the same psychologist.

**Fig. 2 Fig2:**
[figure not shown]
Flow diagram

All participants will receive four study questionnaires in total; one at baseline (T0, about 6 weeks prior to their next full dermatological consultation at the HRC), one 4 weeks after their HRC consultation (which occurs soon after their third telephone session for those in the intervention group) (T1), and again 1 week after their subsequent full HRC consultation 6 months later (T2), and 12 months later (T3) (see Fig. 2). The 12 month assessment (T3) will assess longer-term effects of the intervention, but is only planned if effectiveness of the intervention is demonstrated at 6 months. Participants who do not complete and return the study questionnaires in the specified time period will be contacted by the research team via telephone or email, as a reminder about the study.

### Outcome measures

The primary outcome will be based on the third questionnaire at 6 months (T2).

### Effect evaluation

Table 2 provides an overview of the measures of efficacy, economic evaluation, and timing of measurement.

**Table 2 Tab2:** Measures and timing of assessment in the Melanoma care study

Variables	Measures	Baseline (T0)	T1^*^	T2^Φ^	T3^‡^
Fear of new or recurrent melanoma	Fear of Cancer Recurrence Inventory	✓	✓	✓	✓
Depression, anxiety, stress and depression	Depression Anxiety and Stress Scales (DASS-21)	✓	✓	✓	✓
Health related quality of life	AQOL-8D and FACT-M	✓		✓	✓
Knowledge	A 9 item scale specifically developed for this study	✓	✓	✓	✓
Healthy behavioural adjustment to melanoma risk	The Sun Protection Habits Scale (SPHS) and adapted items for sun protection and skin self examination	✓		✓	✓
Satisfaction with clinical care	Consultation Satisfaction Questionnaire (CSQ)	✓	✓	✓	
Unmet information and support needs	Modified Cancer Survivors’ Unmet Needs (CaSUN)	✓	✓	✓	
Resource use and cost outcomes	Items developed for this study (resource use) and Medicare data (PBS and MBS)	✓		✓	✓
Health literacy		✓			
Medical record	From the melanoma clinics’ databases	✓		✓	✓
Process evaluation	Developed for use in this study.	✓		✓	
Demographic and other risk factors	Age, gender, marital status, number of children, education, income, occupation	✓			

^*^T1: 6 weeks after randomisation, ^Φ^T2: 7 months after randomisation, ^‡^T3: 13 months after randomisation

#### Primary outcome measure

The primary outcome in this study is the level of self-reported fear of new or recurrent melanoma assessed using the severity sub-scale of a modified (i.e. melanoma-specific) version the 42-item Fear of Cancer Recurrence Inventory (FCRI). (Simard & Savard 2009) A higher FCRI score is indicative of greater FCR. The other six sub-scales of the FCRI (triggers, psychological distress, functional impairment, reassurance, insight, and coping strategies) will also be analysed as outcomes. Previous research has demonstrated high internal consistency (α = 0.75–0.91) and reasonable temporal stability (r = 0.58–0.83) of the sub-scales of the FCRI, as well as good criterion validity when compared with other self-report scales assessing fear of cancer recurrence (r = 0.68 to 0.77) or related constructs (Simard & Savard 2009).

#### Secondary outcome measures

*General depression, anxiety and stress*: measured using the short version of the Depression Anxiety and Stress Scales (DASS-21) (Lovibond & Lovibond 1995). The DASS-21 is a set of three 7-item self-report scales designed to measure the emotional states of depression, anxiety and stress. The total score of each subscale of the DASS-21 is classified from “normal” to “extremely severe”.

*Health-related quality of life (HRQoL)*: HRQoL will be assessed using two measures. The Assessment of Quality of Life—8 Dimensions (AQoL-8D) is a 35-item health-related QoL preference-based measure, specifically developed for mental health, with norms for the Australian population by age and sex. The AQOL-8D produces utilities for quality-adjusted life year (QALY) estimation, used in economic evaluations (Richardson et al. 2009; Richardson & Iezzi 2010). The Functional Assessment of Cancer Therapy (FACT-M) (Cormier et al. 2005) (melanoma) contains the 27 core items of the FACT–G (general), plus an additional 24 melanoma-specific items encompassing three domains: physical well-being (20 items), emotional well-being (3 items), and social well-being (1 item). The FACT-M yields both a total QoL score as well as domain scores. An algorithm is available to transform FACT-M scores to utilities for QALY estimation, thereby facilitating a comparison of health economic outcomes.

*Behavioural adjustment to melanoma risk*: Three melanoma-related behaviours will be assessed: sun exposure, sun protection, and skin self-examination. Three items from the consensus-based set of core survey items developed by Glanz et al. will be used to assess sun exposure (Glanz et al. 2008). One item will assess instances of sunburn in the past 12 months. The Sun Protection Habits Scale (Glanz et al. 2002) will be adapted to assess the use of seven sun protection behaviours (e.g. sunscreen use). Engagement in skin self-examination will be assessed with three items adapted from Manne et al. (Manne & Lessin 2006).

*Satisfaction with clinical care*: will be measured using the Consultation Satisfaction Questionnaire (CSQ) (Baker 1990). The CSQ is comprised of 18 items assessing: general satisfaction (3 items); professional care (7 items); depth of relationship (5 items); and perceived time (3 items).

*Unmet information and support needs*: will be assessed using an adapted version of the Cancer Survivors’ Unmet Needs (CaSUN) questionnaire, which includes needs related to information, medical, emotional, quality of life, life perspective (Hodgkinson et al. 2007b; Hodgkinson et al. 2007c). The CaSUN includes 35 unmet need items, 6 positive change items and an open-ended question.

*Knowledge*: A purposely-designed set of items was developed to assess knowledge of specific issues covered in the booklet ‘*Melanoma: Questions and Answers’.*

#### Covariates

Information on demographic factors including age, sex, marital status, education, number of children, health literacy and total family income will be collected. In addition, clinical information such as their doctor’s name, presence of dysplastic nevus syndrome, presence of high penetrance genetic mutation, family history of melanoma, dates of personal melanoma diagnoses, melanoma American Joint Committee on Cancer (AJCC) stage, Breslow thickness, site of the melanoma(s), and other major illnesses will be extracted from the clinic records.

### Sample size

Sample size calculation has been based on 80 % power and a two-sided α = 0.05 test. Because there is no existing literature or clinical opinion to provide an estimate of the minimal clinically important difference, a standardised mean difference (Cohen’s *d*) of 0.5 was employed, which is a moderate effect size and has been found to be applicable to a wide variety of patient-reported outcomes (Norman et al. 2003). Based on these values, the sample size required is 64 per group. When taking into account the expected attrition rate of 20 %, the sample size required is 77 per group (154 total).

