**Methods:**

The intervention is comprised of a newly-developed psycho-educational booklet and three telephone sessions delivered by a trained psychologist. A total of 154 melanoma survivors at high risk of developing new primary disease who are attending one of three melanoma high risk clinics in New South Wales, Australia, will be recruited. Participants will be assessed at baseline (6 weeks before their high risk clinic dermatological appointment), and then 4 weeks and 6 months after their appointment. If effectiveness of the intervention is demonstrated at 6 months, an additional assessment at 12 months is planned. The primary outcome is fear of new or recurrent melanoma, as assessed by the Fear of Cancer Recurrence Inventory (FCRI). Secondary outcomes include anxiety, depression, unmet supportive care needs, satisfaction with clinical care, knowledge, behavioural adjustment to melanoma risk, quality of life, and cost-effectiveness of the intervention from a health system perspective. Following the intention-to-treat principle, linear mixed models will be used to analyse the data to account for repeated measures. A process evaluation will also be carried out to inform and facilitate potential translation and implementation into clinical practice.

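### The 20 % attrition allowance is too small: 77 per group leaves 61.6, not the 64 per group that the stated 80 % power requires

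*Protocol article*

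**What the plan says.** The Sample size section of the protocol article gives the whole calculation in one paragraph. On error rates it states: "Sample size calculation has been based on 80 % power and a two-sided α = 0.05 test". For the effect, a Cohen's d "of 0.5 was employed, which is a moderate effect size", chosen because no minimal clinically important difference was available. The result before attrition is "the sample size required is 64 per group". With an expected attrition rate of 20 %, it concludes that "the sample size required is 77 per group (154 total". The formula for the attrition allowance is not written out.

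The same total is the recruitment target in the Methods paragraph of the abstract: "A total of 154 melanoma survivors at high risk of developing new primary disease". Under Outcome measures, the primary outcome is taken from the 6-month questionnaire (T2), so the losses that matter are those up to T2.

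**The concern.** An attrition rate is the share of randomised participants who are lost. To finish with a given number after losing 20 %, that number is divided by 0.80. Multiplying by 1.20 adds 20 % of the smaller number, and removing 20 % of the larger one then takes away more than was added. The step from 64 to 77 looks like the multiplication.

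If so, the trial's headline size does not meet its own requirement at its own attrition rate, and the 80 % power is overstated. The allowance also matters to this trial in particular. The Limitations section says that participants are not screened for psychological need and that those without such needs may be more inclined to withdraw, while the Strengths section claims sufficient power.

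**Working it through.** **Inputs**, all from the Sample size section: power 80 %; alpha 0.05, two-sided; d = 0.5 (so SD = 1 on this scale); attrition 20 %; 64 per group before attrition; 77 per group and 154 in total after it. Equal allocation is implied by the equal group sizes.

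**Step 1: reproduce the 64.**
- Normal approximation: n = 2 × [(z₀.₉₇₅ + z₀.₈₀) / d]² = 62.8, so 63 per group.
- Two-sample t-test (non-central t): n = 63.77, so 64 per group. This is the stated figure.
- A one-sided test would need 50.15, so 51. The stated two-sided test is therefore the one used.

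**Step 2: reproduce the 77.**
- 64 × (1 + 0.20) = 76.8, so 77 per group and 154 in total. This matches the protocol exactly.
- 64 / (1 − 0.20) = 80 per group and 160 in total. This does not match.
- Rounding does not explain the gap: the unrounded 63.77 / 0.80 = 79.7 also rounds up to 80.

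**Step 3: what 154 leaves at 20 % attrition.**
- 77 × 0.80 = 61.6 per group, against 64 needed: short by 2.4.
- 154 × 0.80 = 123.2 in total, against 128 needed: short by 4.8.
- The normal-approximation requirement of 63 is not met either.

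**Step 4: power for d = 0.5, two-sided alpha 0.05, two-sample t-test.**

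| Completers per group | Power |
|---|---|
| 64 | 80.1 % |
| 62 | 78.9 % |
| 61.6 | 78.6 % |
| 61 | 78.2 % |

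By the normal approximation, power at 61.6 per group is 79.2 %, still below 80 %. The effect detectable with 80 % power at 61.6 per group (t-test) is d = 0.509.

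**Step 5: the attrition that 154 can absorb.**
- To keep 64 per group: 1 − 64/77 = 16.9 %.
- To keep exactly 80 % power (63.77 per group): 1 − 63.77/77 = 17.2 %.

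Either way, the limit is about 17 %, not 20 %.

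**The case against.** The strongest reply is that the shortfall has no practical consequence for the analysis actually planned. The Statistical analyses section specifies linear mixed models by intention to treat, and Table 2 has the FCRI measured at T0, T1 and T2. Participants lost before T2 would still contribute earlier data, and baseline information can reduce the residual variance. If baseline is used efficiently, the effective standardised difference becomes 0.5 / √(1 − r²), where r is the baseline-to-T2 correlation. With r = 0.2, this is 0.510, and power at 61.6 per group is 80.2 %. The Primary outcome measure section cites temporal stability of 0.58 to 0.83 for the FCRI sub-scales. The interval behind that range is not given, so carrying it over to 6 months is an assumption, but r = 0.2 is a low bar.

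It can also be said that the inputs are coarser than the error. The d of 0.5 is a convention and the 20 % is an expectation; 1.5 percentage points of power are small beside the uncertainty in either. Finally, the multiplication by 1.2 is inferred, since no formula is given.

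Most of this stands as a statement about consequence. It does not make 77 correct. The Sample size section takes no credit for baseline or repeated measures: 64 is the plain two-sample t-test number, and the attrition allowance is applied directly to it. Nor does the shortfall depend on how 77 was obtained, because 77 × 0.80 is below 64 whatever the formula.

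**Conclusion.** The point holds. On the section's own inputs, 154 participants, 20 % attrition and 80 % power cannot all be true. At 20 % attrition, the stated size gives 78.6 % power for d = 0.5, about 1.5 percentage points below the 80.1 % at 64 per group. The size consistent with the stated power and attrition is 80 per group, 160 in total, which is 6 more than planned.

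This rests on equal allocation, the same attrition in both arms, attrition counted as a share of those randomised, and an unadjusted two-sample t-test among participants with a T2 score, which is the basis on which the 64 was derived. The error is one of arithmetic and description. It does not threaten the validity of the trial, and the planned mixed model probably recovers the lost power.

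**What to change.** Keep 154 and correct the statement in the Sample size section, for example: *Randomising 77 per group (154 in total) leaves about 61.6 per group at 20 % attrition, which gives 78.6 % power for d = 0.5 in a two-sided two-sample t-test at the 5 % level; 80 % power is retained if attrition is no more than about 17 %.* A clause may be added that the planned mixed model, by using baseline and repeated measures, is expected to raise power above this figure, provided the correlation assumed is stated.

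The cost is one sentence and a slightly less favourable power figure; nothing in the design or conduct changes.

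If 80 % power at 20 % attrition is to stand on the present t-test basis, the target must be 80 per group (160 in total), in both the Sample size section and the abstract. That costs 6 further participants, 3 of whom would receive the intervention.

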### Economic evaluation

A trial-based economic evaluation will be conducted from a health system perspective. The following items for measurement of costs will be identified, measured and valued:Cost of the production of the psycho-educational booklet;Psychologist costs;Number of telephone sessions and duration;Access to external psychological services;Hospital admissions; andPrescribed medications.

Health service use and costs of the intervention will be estimated using three methods: 1) the Australian Medicare Benefits Schedule (MBS) and Pharmaceutical Benefits Scheme (PBS) databases (individual informed consent was obtained to access to these individual-level data); 2) self-report regarding use of healthcare resources not covered by the MBS and PBS databases; and 3) trial records, including research team and psychologist records related to intervention delivery.

In the economic evaluation, total and mean costs for the intervention and control group will be reported in a disaggregated format. Total and mean severity outcomes (FCRI Severity subscale score and AQOL-8D utility (quality of life score)) will be reported for the intervention and control groups. The difference in mean scores between the two groups will be assessed with appropriate statistical tests. Incremental cost-effectiveness ratios will be calculated in terms of: a) the incremental cost per participant achieving a significant decrease in mean FCRI Severity score (0.5 of the SD on the FCRI Severity subscale which is considered to be a meaningful change) (Norman et al. 2003); and b) the incremental cost per quality-adjusted life year (QALY) gained in the intervention group compared with the control group. Results will be plotted on a cost-effectiveness plane. Bootstrapping will be used to estimate a distribution around costs and health outcomes and to estimate the confidence intervals around the incremental cost-effectiveness ratio (Medical Services Advisory Committee MSAC 2000; Drummond et al. 2005; Gold et al. 1996). One-way sensitivity analysis will be conducted around key variables including the QoL instruments, and a cost-effectiveness acceptability curve (CEAC) will be plotted (Medical Services Advisory Committee MSAC 2000; Drummond et al. 2005; Gold et al. 1996).

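### The planned bootstrap interval for the cost-per-QALY ICER cannot be read if replicates fall on both sides of zero effect; a net monetary benefit interval would stay readable beside the planned plane and CEAC.

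*Protocol article*

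**What the plan says.** The Economic evaluation section of the protocol article defines two ICERs. One is the cost per participant whose FCRI Severity score falls by at least half an SD. The other is "the incremental cost per quality-adjusted life year (QALY) gained in the intervention group compared with the control group".

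For uncertainty it plans a cost-effectiveness plane, a bootstrap distribution of costs and outcomes, a CEAC, and bootstrapping "to estimate the confidence intervals around the incremental cost-effectiveness ratio". That last commitment carries no condition. The section does not say how the interval is formed, or what is reported if replicates fall in more than one quadrant. Net monetary benefit is not named.

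The Sample size section rests on a standardised difference "of 0.5 was employed, which is a moderate effect size" and concludes that "the sample size required is 77 per group (154 total"). It states no power for costs, QALYs or the responder outcome.

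**The concern.** An ICER is a cost difference divided by an effect difference. As the effect difference passes through zero, the ratio jumps between very large positive and very large negative values. The sign is also ambiguous. A negative ratio arises when the intervention is better and cheaper (dominant) and when it is worse and dearer (dominated). A positive ratio arises when it is better and dearer, and when it is worse and cheaper. Once a material share of replicates lies on each side of zero effect, ordering the ratios no longer orders value for money, and the two limits have no clear meaning.

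The Study aims and hypotheses section states that the intervention will be cost-effective from a health system perspective, and the Strengths section says the evidence is meant for decisions on adoption and reimbursement. A reader who quotes the ICER interval alone could take a negative limit as good news when part of it comes from replicates in which the intervention is dominated.

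**Working it through.** **The plan's own figures.** A two-sample t-test with d = 0.5, a "two-sided α = 0.05 test" and 80% power needs 63.77, rounded up to 64 per group. This reproduces "the sample size required is 64 per group". The 77 reproduces as 64 x 1.2 = 76.8. With 20% attrition, 77 x 0.8 = 61.6 per group are analysed, and that figure is used below.

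**Cost-per-QALY ratio: inputs.**
- From the article: 61.6 analysed per arm. T2 is 7 months after randomisation, and AQoL-8D is collected at T0 and T2 but not T1 (Table 2).
- Assumed, because the article gives none of them: utility SD 0.16; T0-T2 correlation 0.7; QALYs from a straight line between T0 and T2; true utility gains at T2 of 0.01 to 0.08.

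**Formulas.**
- QALY difference = (7/12)/2 x gain = 0.2917 x gain.
- SE = (7/12)/2 x SD x sqrt(1 - r²) x sqrt(2/n) = 0.2917 x 0.16 x sqrt(0.51) x sqrt(2/61.6) = 0.0060.
- z = QALY difference / SE. The share of the sampling distribution below zero is Phi(-z).
- Chance that more than 2.5% of replicates lie on each side of zero (equivalently, that the 95% interval for the effect includes zero) = Phi(1.96 - z) - Phi(-1.96 - z).

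| Utility gain | QALY difference | z | Below zero | Chance of crossing |
|---|---|---|---|---|
| 0.01 | 0.0029 | 0.49 | 31% | 92% |
| 0.02 | 0.0058 | 0.97 | 17% | 84% |
| 0.03 | 0.0088 | 1.46 | 7% | 69% |
| 0.05 | 0.0146 | 2.43 | 0.8% | 32% |
| 0.08 | 0.0233 | 3.89 | <0.1% | 3% |

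A bootstrap simulation of 2,000 trials gave 91%, 81%, 68% and 32% at gains of 0.01, 0.02, 0.03 and 0.05. A smaller one (400 trials per gain, 500 resamples) gave 92%, 79%, 65% and 31%. Varying the SD over 0.12 to 0.20 and the correlation over 0.5 to 0.85 moves the chance at a gain of 0.02 between 58% and 90%. The factor (7/12)/2 appears in both the QALY difference and its SE, so it cancels in z. With two time points, the 7 months themselves do not drive the result.

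**FCRI-responder ratio.** Inputs: the sub-scale temporal stability of 0.58 to 0.83 given under Primary outcome measure, 61 to 64 per group, and an assumed normal change score with no mean change in controls. In SD units the change-score SD is sqrt(2(1 - r)). The responder proportions are Phi(-0.5/SD) in controls and Phi((-0.5 + d)/SD) under the intervention.
- At d = 0.5, r = 0.58, n = 61: 0.293 against 0.500, z = 2.40, chance of crossing 33%.
- At d = 0.5, r = 0.83, n = 64: 0.196 against 0.500, z = 3.82, chance 3%.
- At d = 0.2 the range is 71 to 85%.

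**What a crossing interval looks like.** This is an illustration on assumed inputs: n = 64, QALY SD 0.1, standardised QALY effect 0.2, cost difference 500, cost SD 3,000. The point ICER is 500/0.02 = 25,000. The percentile interval runs from about -259,000 to 305,000. Of all replicates, 15% are dominant and 11% dominated, and both groups supply the negative values. From the same replicates, the probability of cost-effectiveness at an assumed threshold of 50,000 is 0.69, which is one point on a CEAC.

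**The case against.** The strongest reply is that the plan does not depend on this interval. The same section promises a plane, a bootstrap distribution of costs and outcomes, and a CEAC, and all three stay readable across quadrants. This stands. A reader might infer that the ICER interval is the only statement of uncertainty, or that the cost-effectiveness hypothesis could not be assessed. The document supports neither reading, since the CEAC already gives the share of replicates with positive net benefit at each threshold.

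A second reply is that the article does not say ratios will be sorted and percentiles taken, and that quadrant handling may sit in a fuller analysis plan. This stands in part. The missing detail is no fault in a condensed article, but the interval itself is promised without condition, and the sign ambiguity affects any single pair of ICER limits. Nor is the interval numerically wrong: in the 400-trial simulation (assumed gamma costs with mean 1,500, SD 2,000 and difference 800) coverage was 93 to 97%. The difficulty is interpretation.

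A third reply is that the probabilities rest on chosen inputs. This also stands. With an SD of 0.16, gains of 0.01 to 0.03 are standardised effects of only 0.06 to 0.19, while a gain of 0.08 (0.5 SD) brings the chance down to about 3%. The article claims no effect size for utility. The figures also leave out T3, when AQoL-8D is collected again if effectiveness is shown at 6 months.

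**Conclusion.** This is a minor point that holds conditionally. If replicates fall on both sides of zero effect, the planned ICER interval cannot be read, while the plane and CEAC remain valid.

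Crossing is plausible for the cost-per-QALY ratio because the trial is not sized for QALYs. Under the stated assumptions the chance is about 80 to 84% at a utility gain of 0.02, about 32% at 0.05, and lower beyond that. It is less likely for the FCRI-responder ratio at the design effect (3 to 33%), although not if the true effect is small.

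A reader might go further and call crossing likely simply because of the trial's size. The document does not support that, because it gives no utility effect, utility SD or correlation, and the answer turns on them.

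**What to change.** In the Economic evaluation section, replace the interval for the cost-per-QALY ICER with incremental net monetary benefit and its bootstrap 95% interval, at stated willingness-to-pay values per QALY. Resample each participant's cost and QALY as a pair, within arm. Keep both ICERs as point estimates with the plane and CEAC, and give the share of replicates in each quadrant.

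Report an interval for the FCRI-responder ICER only if its replicates do not cross zero effect, and state what share counts as crossing (2.5% on the far side is the level used here). A rule of no replicate at all would be too strict. On the continuous score, at an observed standardised effect of 0.5 with 64 per group, 0.23% of replicates fall below zero, so the chance of at least one in 1,000 is 1 - (1 - 0.0023)^1000, about 90%.

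The change takes a few sentences and uses the bootstrap replicates already planned. The downside is having to state one or more willingness-to-pay values.
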